#### **III-3. Exploratory objectives**

The study also aims to:

- Analyse the effect of convalescent plasma on SARS-CoV-2 viral load.
- Describe the course of anti-SARS-CoV-2 spike antibody levels in blood (provisional).
- Analyse the SARS-CoV-2 whole genome sequence.
- Determine whether persistently-infected immunosuppressed individuals are a source of infectious viral variants.
- Analyse the association between receipt of CCP and development of infectious SARS-CoV-2 viral variants.

#### **III-4. Study endpoints**

**The primary endpoint** is the proportion of participants with (1) at least one overnight stay in hospital for progressive COVID-19 symptoms, or (2) who died, by day 28 after randomisation. COVID19 related

hospitalizations will be adjudicated using a three member panel. Each member will independently come to a decision on whether the hospitalization or decision to extend a hospitalisation was or was not related to COVID-19 using as much information that could be provided such as hospital discharge forms but remain blinded for the randomization group. Classification of whether the hospitalization was due to COVID-19 will be by majority decision of the panel.

Secondary outcome measures include core outcomes from the meta-core outcome set (COS) for hospitalised patients (<http://www.comet-initiative.org/Studies/Details/1538>), and the WHO progression scale. There is no COS for patients with COVID-19 managed in the community. Viral outcome measures will enable assessment of mechanism.

**Secondary endpoints include:**

**Efficacy:**

1. Proportion of participants with hospitalisation for progressive COVID-19 symptoms, or death by day 14 after randomisation (stages 4 to 9 of the WHO scale)
2. Proportion of participants with hospitalisation for progressive COVID-19 symptoms requiring O2 support\*, or death by day 14 and 28 after randomisation (stages 5 to 9 of the WHO scale)
3. All-cause mortality by day 28, 90 and 180 after randomisation
4. Proportion of patients with supplemental oxygen by day 14 and 28 after randomisation
5. Proportion of patients with non-invasive ventilation by day 14 and 28 after randomisation
6. Proportion of patients with intubation and mechanical ventilation by day 14 and 28 after randomisation
7. Change in 10-point WHO Clinical Progression Scale score by day 14 and 28 after randomisation (see below)
8. Duration of hospital admission censored at 28 days after randomisation (for participants reaching primary endpoint)
9. Proportion of patients with admission to ITU by day 14 and 28 after randomisation
10. Duration of ITU admission censored at 28 days after randomisation
11. Proportion of patients with long COVID-19 symptoms and time to recovery assessed by questionnaire at days 28 and 180 post randomisation
12. Health-related quality of life assessed using the EQ-5D-5L at 28 and 180 days after randomisation

\* O2 support requirement based on O2 saturation level on room air  $\leq 93\%$  and/or Respiratory Rate  $> 30$

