**Table 2. 10-point WHO Progression scale**

| Patient state                  | Descriptor                                                                                                               | Score |
|--------------------------------|--------------------------------------------------------------------------------------------------------------------------|-------|
| Uninfected                     | Uninfected; no viral RNA detected                                                                                        | 0     |
| Ambulatory                     | Asymptomatic; viral RNA detected                                                                                         | 1     |
|                                | Symptomatic; independent                                                                                                 | 2     |
|                                | Symptomatic; assistance needed                                                                                           | 3     |
| Hospitalised: moderate disease | Hospitalised; no oxygen therapy*                                                                                         | 4     |
|                                | Hospitalised; oxygen by mask or nasal prongs                                                                             | 5     |
| Hospitalised: severe disease   | Hospitalised; oxygen by NIV or high flow                                                                                 | 6     |
|                                | Intubation and mechanical ventilation, pO 2 /FiO 2 ≥150 or SpO 2 /FiO 2 ≥200 | 7     |
|                                | Mechanical ventilation pO 2 /FiO 2 <150 (SpO 2 /FiO 2 <200) or vasopressors  | 8     |
|                                | Mechanical ventilation pO 2 /FiO 2 <150 and vasopressors, dialysis, or ECMO                        | 9     |
| Dead                           | Dead                                                                                                                     | 10    |

ECMO=extracorporeal membrane oxygenation. FiO2=fraction of inspired oxygen. NIV=non-invasive ventilation. pO2=partial pressure of oxygen. SpO2=oxygen saturation. \*If hospitalised for isolation only, record status as for ambulatory patient.

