### **Secondary endpoints analysis**

Secondary endpoints include the following:

- Proportion of hospitalisation for progressive COVID-19 symptoms, or death by day 14 after randomisation
- Proportion of hospitalisation for progressive COVID-19 symptoms requiring O2 support, or death by day 14 and 28 after randomisation
- All-cause mortality by day 28, 90 and 180 after randomisation
- Proportion of patients with supplemental oxygen by day 14 and 28 after randomisation
- Proportion of patients with non-invasive ventilation by day 14 and 28 after randomisation
- Proportion of patients with intubation and mechanical ventilation by day 14 and 28 after randomisation
- Change in 10-point WHO Clinical Progression Scale score at 14 and 28 days after randomisation
- Duration of hospital admission censored at 28 days after randomisation (for participants reaching primary endpoint)
- Proportion of patients with admission to ITU by day 14 and 28 after randomisation
- Duration of ITU admission censored at 28 days after randomisation
- Proportion of patients with long COVID-19 symptoms and time to recovery assessed by questionnaire at days 28 and 180 post randomisation
- Health-related quality of life assessed using the EQ-5D-5L at 28 and 180 days after randomisation

Binary outcomes will be analysed using Z-tests or Fisher's exact tests. When appropriate Risk differences will also be provided with their 95% confidence intervals. As a sensitivity analysis, generalized linear mixed models (with logit link) with a random centre effect will be performed. Time-to-event outcomes will be analysed using log-rank tests with sensitivity analyses based on Cox regression models with a random centre effect (results will be expressed as hazard ratios with 95% confidence interval). Finally, quantitative outcomes will be analysed using Student's t-tests or Mann-Whitney tests, as appropriate. Sensitivity analyses will consist in mixed linear regression with a random centre effect (results will be expressed as mean differences with 95% confidence interval).

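### Secondary endpoints 1 and 2 include death, but the WHO-scale ranges printed beside them end at stage 9 while Table 2 scores death as 10

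*Protocol*

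**What the plan says.** Protocol section III-4 lists twelve secondary efficacy endpoints. The first two are composites of hospitalisation and death, each followed by a bracketed WHO range.

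- Endpoint 1: hospitalisation for progressive COVID-19, "or death by day 14 after randomisation (stages 4 to 9 of the WHO scale").
- Endpoint 2: the same with a need for oxygen, "or death by day 14 and 28 after randomisation (stages 5 to 9 of the WHO scale"). A footnote defines that need by room-air saturation of 93% or less and/or a respiratory rate above 30.

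The scale is set out in "Table 2. 10-point WHO Progression scale". Score 4 is "Hospitalised; no oxygen therapy" and score 5 is "Hospitalised; oxygen by mask or nasal prongs". Score 9 is mechanical ventilation with a low oxygenation ratio "and vasopressors, dialysis, or ECMO". Death has its own row, scored 10.

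Section X-3 (Secondary endpoints analysis) restates both endpoints without any stage range. The first reads "Proportion of hospitalisation for progressive COVID-19 symptoms, or death by day 14 after randomisation".

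**The concern.** In both endpoints the bracket comes after the whole composite, including the words on death, so it reads as the translation of that composite into WHO scores. As a translation it is wrong: it covers the living hospitalised states and omits the dead.

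At stake is the coding of death in two efficacy endpoints. If the endpoints were derived from the score range, some or all patients who die by the cut-off day would be analysed as free of the event. The worst outcome would then count as a success, and a true difference in mortality between the arms would be removed from the composite or diluted.

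**Working it through.** No sample-size or power formula applies. The check maps the endpoint wording onto Table 2 and then follows deaths through the possible derivation rules.

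**Step 1. Mapping the wording to scores (III-4 against Table 2).**

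| Component | Table 2 scores |
|---|---|
| Hospitalised, with or without oxygen | 4 to 9 |
| Hospitalised, on oxygen or more | 5 to 9 |
| Dead | 10 |

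Hospitalised or dead is therefore 4 to 10. Hospitalised on oxygen or dead is 5 to 10. The stated ranges, 4 to 9 and 5 to 9, match the hospitalised part alone, and 10 lies in neither.

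**Step 2. Could the score plausibly be used?** Table 3 schedules the Clinical Progression Scale at day 1, day 3, day 14, day 28 and the hospitalisation visit. Section VI-4-2 asks for it at each visit and at the time of death, so a patient who dies should carry a 10. Table 3 has no vital-status tick at day 14, although VI-4-2 lists vital status at each visit. The score is thus an available source for a day-14 endpoint, but not the only one.

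**Step 3. What happens to a death under each rule.** Three hypothetical patients, all dead by the cut-off day:

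- A: ambulatory scores only, then 10 (death outside hospital).
- B: score 4 in hospital, then 10.
- C: score 6 in hospital, then 10.

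| Rule applied to the stated range | Endpoint 1 (4 to 9) | Endpoint 2 (5 to 9) |
|---|---|---|
| Score at the day-14 or day-28 visit | A, B, C all lost | A, B, C all lost |
| Worst score reached | A, B, C all lost, since the worst score is 10 | A, B, C all lost |
| Any recorded score in the range | A lost; B and C counted | A and B lost; C counted |
| Verbal definition (III-4 wording, X-3) | all counted | all counted |

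**Step 4. Would another rule recover the lost deaths?** The missing-data rule in X-3 treats missing binary outcomes as failures only in the interim and primary final analyses, with no imputation for secondary outcomes. In any case a recorded score of 10 is not missing.

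**Step 5. Reach.** The primary endpoint, in III-4 and X-3, carries no WHO range and includes death. The sample size and the interim re-estimation rest on that endpoint, so neither is touched.

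**The case against.** The strongest reply is that the bracket was meant as a gloss on the hospitalisation component only. The version-history entry for V2.3 says that the WHO levels were added to mark severe COVID-19 with or without oxygen, and items 1 and 2 of the objectives in III-2 name hospitalisation without death. Stages 4 to 9 and 5 to 9 are exactly those living states. Section X-3 gives both endpoints with death and without a range, and vital status and hospitalisation are collected as items separate from the scale. This is a plausible account of the intent, and it limits the consequence. It does not remove the fault, because the brackets as printed qualify the whole composite.

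A reader might infer more than the documents support:

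- **That the endpoints will be derived from the score.** The protocol does not say so. Neither endpoint can be derived faithfully from the score alone: stage 4 does not require progressive COVID-19 symptoms, and the oxygen criterion for endpoint 2 is a saturation and respiratory-rate rule.
- **That every death outside hospital would be misclassified.** Under a rule of any score in the range, a patient with an earlier in-range stay who later dies at home still counts.
- **That the visit score would be used.** Both endpoints count events up to the cut-off day, which fits poorly with a score read at a single visit.

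Also, X-3 describes secondary analyses as exploratory, and all-cause mortality by day 28 is a separate endpoint, so deaths would not vanish from the report.

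**Conclusion.** The point holds as an internal contradiction: two efficacy endpoints are worded to include death and carry score ranges that exclude it. This follows from III-4 and Table 2 alone.

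The consequence is conditional. If the brackets are used for derivation, the loss runs from deaths with no earlier in-range score (any-score rule) to all deaths by the cut-off day (visit-score or worst-score rule). If the verbal definition is followed, no death is lost. The loss cannot be put in percentage points, since the protocol states no expected death rate for trial patients by day 14 or 28 and no split between deaths in and out of hospital.

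A reader might go on to conclude that the trial's main result is at risk or that the secondary results will be biased. The documents support neither. The primary analysis, interim analysis and sample size do not use these ranges, and X-3 already holds a correct definition. The correction should still be made, because it is cheap and concerns how death is counted.

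**What to change.** Make one of two changes in III-4:

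1. Change the brackets to stages 4 to 10 for endpoint 1 and stages 5 to 10 for endpoint 2; or
2. Keep 4 to 9 and 5 to 9, but attach them explicitly to the hospitalisation component and state that death from any cause by the cut-off day is an event.

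Under either option, keep the requirement for progressive COVID-19 symptoms and the oxygen-support criterion as the definition, with the WHO stages as a cross-reference. Do not redefine the endpoints as a worst WHO score. That would count hospital stays not due to progressive COVID-19 and displace the oxygen criterion, and with the present ranges it would drop every death.

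The cost is two figures, or one clause, in the protocol, carried through to any SAP and programs that repeat the ranges. Data collection and sample size do not change.

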**Safety:**

13. Number of serious Adverse Events at 72 hours after randomisation (Grade 3/4 adverse events and AE unexpected for their nature, onset, evolution, severity or frequency)
14. Arterial and venous thromboembolic events at 28, 90 and 180 days after randomization

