## I. STUDY PRESENTATION - CONTEXT

The COVIC-19 study is a prospective randomized clinical study evaluating the benefit of COVID-19 convalescent plasma (CCP) with a very high antibody titre administered early, on an outpatient basis, to vulnerable patients to prevent the progression of a COVID-19 disease to a severe form requiring hospitalization. The vulnerable patients concerned by this study are patients with recently diagnosed COVID-19 disease who do not need hospitalisation and who are: at least 70 years old; younger patients with risk factors for severe COVID-19; and patients with primary or secondary immunodeficiency. Patients randomized to the treatment arm will receive 2 units of CCP with high titre anti-SARS-CoV-2 antibody on an outpatient basis within 7 days of the onset of symptoms of COVID-19. Patients in the control group will not receive a specific intervention.

This study is based on growing evidence for the effectiveness of passive immunotherapy, by transfusion of CCP or administration of monoclonal antibodies, as long as treatment is carried out early after the diagnosis of the disease. In a recent randomized clinical trial in Argentina by Libster et al, the administration of CCP less than 3 days after the onset of symptoms of COVID-19 in vulnerable patients halved the risk of developing severe COVID-19 disease compared to a control group (16% after CCP transfusion vs. 31% without transfusion). Similar findings were recently reported in a clinical trial coordinated by the John Hopkins Hospital (USA). A third randomized trial found similar results as well for patients included less than 5 days after symptoms initiation. A 4th study did not confirm this efficacy of CCP, with however inclusion criteria that differed significantly (patients recruited in emergency rooms).

Importantly, a significant antibody dose response was observed. Likewise, the early administration of monoclonal anti-SARS-CoV-2 antibodies in mono- or bitherapy has been associated with a decrease in the frequency of hospitalization for COVID-19 disease.

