#### **III-2. Secondary objectives**

The secondary objectives of the study are as follow:

To evaluate the efficacy of COVID-19 convalescent plasma on

1. Hospitalisation for severe COVID-19 by day 14 after randomisation
2. Hospitalisation for severe COVID-19 requiring O2 support by day 14 and 28 after randomisation
3. All-cause mortality by day 28, 90 and 180 after randomisation
4. Requirement for supplemental oxygen by day 14 and 28 after randomisation
5. Requirement for non-invasive ventilation by day 14 and 28 after randomisation
6. Requirement for mechanical ventilation by day 14 and 28 after randomisation
7. The change in WHO Clinical Progression Scale score by day 14 and 28 after randomisation
8. The duration of hospital stay
9. The need for admission to ITU by day 14 and 28 after randomisation
10. The duration of ITU stay
11. Cases of long COVID-19 symptoms and the time to recovery
12. Health-related quality of life

To analyse the safety of COVID-19 convalescent plasma with regard to:

1. Serious adverse events (Grade 3/4 adverse events) and AE unexpected for their nature, onset, evolution, severity or frequency
2. Arterial and venous thrombotic events

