Any incident or error susceptible to affect the safety or the quality of blood or blood component and to cause adverse effects. It can be related to any step of the blood transfusion chain : blood collection, biological qualification of the blood donation, preparation, conservation, transport, distribution, dispensation, realization of pre-transfusion analyses, use of labile blood product, delay or lack of their transfusion.

Dysfunctions related to information systems and to patients identification are also incidents if they are susceptible to affect the products' safety or quality and to cause adverse reactions.

An incident is qualified as serious when susceptible to cause serious adverse effects.

- **Definition of an Unexpected Adverse Event**

Unexpected side effect is any side effect of the product, nature, severity, frequency or course of which does not agree with the reference safety information given in the summary of product characteristics or in the investigator brochure for the product when the product is not authorized (see chapter IX Undesirable effects).

- **Definition of a new fact**

Any new data that may lead to a reassessment of the ratio of benefits and risks of the research or of the product being researched, to modifications in the use of this product, in the conduct of research, or of documents relating to the research, or to suspend or interrupt or modify the research protocol or similar research.

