### **Safety analysis of intervention**

Safety endpoints include the following:

- Number of serious Adverse Events at 72 hours after randomisation (Grade 3/4 adverse events and AE unexpected for their nature, onset, evolution, severity or frequency)
- Arterial and venous thromboembolic events at 28, 90 and 180 days after randomization

Adverse events and their characteristics will be described using numbers and percentages per treatment arm. The proportion of participants with each of the reported events, as well as the

proportions of participants with at least one SAE will be compared using Fisher's exact tests. The total number of AE/SAEs and SAEs will also be described for each arm, and compared using Poisson models (with a robust error variance if necessary).

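### The 72-hour count of serious adverse events includes unexpected events, which the protocol defines only in relation to the plasma, so this component has no stated reference in the control arm

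*Protocol*

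**What the plan says.** - **Endpoint (III-4, Safety, endpoint 13; repeated in X-3, Safety analysis of intervention).** The first safety endpoint is the number of serious adverse events 72 hours after randomisation, explained in brackets as "Grade 3/4 adverse events and AE unexpected for their nature, onset, evolution, severity or frequency".
- **Objective (III-2).** The matching objective reads "Serious adverse events (Grade 3/4 adverse events) and AE unexpected for their nature, onset, evolution, severity or frequency". The bracket closes after the Grade 3/4 events, so unexpected events are an addition to them and may be of any grade.
- **Definition (IX-1-2).** Under a heading about unexpected adverse events, the text reads "Unexpected side effect is any side effect of the product, nature, severity, frequency or course of which does not agree with the reference safety information" found in the product characteristics or the investigator brochure. No other definition of unexpected appears.
- **Control arm (I).** "Patients in the control group will not receive a specific intervention". IV-1 confirms standard care alone, without blinding or placebo.
- **Analysis (X-3).** For participants, the "proportions of participants with at least one SAE will be compared using Fisher's exact tests", as is the proportion with each reported event. For counts, "The total number of AE/SAEs and SAEs will also be described for each arm, and compared using Poisson models".
- **Safety population (X-1-3).** Only patients who received plasma are named.

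**The concern.** A between-arm count is interpretable only if an event of a given kind would be scored in the same way in either arm. Grade 3/4 events meet that condition. The added component, on the protocol's own definition, does not: it requires a product, and half the trial receives none. In the plasma arm a mild reaction missing from the reference safety information enters a count labelled serious. In the control arm no stated rule lets a comparable event in. Expectedness would also be judged with the allocation known, since only the hospitalisation panel is meant to be blinded (III-4, VIII-2). At stake is the first listed safety endpoint of a phase III trial, which could show more serious events under plasma when severe events are equally frequent.

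**Working it through.** **1. The text side by side**

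| Question | Grade 3/4 events | Unexpected events |
|---|---|---|
| Part of endpoint 13? | Yes (III-4) | Yes, in addition (III-2, III-4) |
| Limited by grade? | Yes | No |
| Reference | Severity of the event | Product reference safety information (IX-1-2) |
| Scorable in plasma arm? | Yes | Yes |
| Scorable in control arm? | Yes | No stated reference; none on the literal definition |

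The general SAE definition in IX-1-2 rests on seriousness and has no expectedness criterion, so it applies equally in both arms. Endpoint 13 uses the same label for something different.

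**2. The plan's own figure**

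The protocol gives no expected value for the 72-hour count. Its sample size (X-2) supplies the number per arm and reproduces with the unpooled two-proportion formula:

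n = (1.960 + 1.282)² × (0.15 × 0.85 + 0.30 × 0.70) / 0.15² = 157.6, so 158 per arm (power 0.901), raised in the plan to 170.

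**3. Size of the effect, under assumptions**

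Let L be the Grade 3/4 event rate at 72 hours, equal in both arms, and u the extra rate of unexpected events in the plasma arm only. Then:

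- expected control count = 170 × L
- expected plasma count = 170 × (L + u)
- rate ratio = (L + u) / L, instead of 1

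Neither L nor u is in the document. I assume L = 3% or 5%, and u from 0 to 5%. The only related figure is in II-5-1: severe or serious transfusion-related events in 0 to 1.3% of plasma recipients in four randomised trials. It concerns severe reactions, so it serves for scale only.

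The last column is the probability that a two-sided 5% Wald test on the log rate ratio of two Poisson counts is significant against plasma. It sums over all pairs of counts and treats pairs with a zero as not significant.

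| L | u | Control count | Plasma count | Rate ratio | P(significant excess) |
|---|---|---|---|---|---|
| 3% | 0 | 5.1 | 5.1 | 1.00 | 0.010 |
| 3% | 0.5% | 5.1 | 5.95 | 1.17 | 0.022 |
| 3% | 1.3% | 5.1 | 7.3 | 1.43 | 0.056 |
| 3% | 2% | 5.1 | 8.5 | 1.67 | 0.106 |
| 3% | 5% | 5.1 | 13.6 | 2.67 | 0.472 |
| 5% | 0 | 8.5 | 8.5 | 1.00 | 0.019 |
| 5% | 0.5% | 8.5 | 9.35 | 1.10 | 0.031 |
| 5% | 1.3% | 8.5 | 10.7 | 1.26 | 0.061 |
| 5% | 2% | 8.5 | 11.9 | 1.40 | 0.098 |
| 5% | 5% | 8.5 | 17.0 | 2.00 | 0.373 |

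With counts this small the test is conservative, so the baseline with no extra events is 1–2% rather than the nominal 2.5% per side. Fisher's exact test at 1.3% extra gives slightly less, 4.6–4.9%.

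**4. Which comparisons are reached**

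The Fisher test on each separately reported event is unaffected, and so is a total of all adverse events, which counts every event whatever its expectedness. The SAE comparisons are affected if SAE in X-3 means the endpoint 13 composite. X-3 lists that composite as the safety endpoint just before describing the tests, but does not say which definition they use.

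**The case against.** **The control arm could be scored.** Endpoint 13 speaks of adverse events, does not cite the IX-1-2 definition and adds terms to it. IX-1-2 defines an adverse event irrespective of its relation to the product, and IX-1-1 lists expected COVID-19 complications against which a control event could be judged. This stands in part: a reader might infer that controls simply cannot be scored, and the protocol does not say that. But the disease list has two entries, hospitalisation and death for progressive COVID-19. It covers serious events only, and nothing tells sites to apply one list to both arms.

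**The extra events are real harm.** Under IX-1-2 each added event is a side effect of plasma, which a safety comparison ought to show. This also stands: the probabilities above are not pure false-positive rates. What is wrong is that a mild reaction is counted as serious, with no equivalent route into the count for controls.

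**The size rests on assumptions.** The largest figures need a 5% rate of unexpected reactions, for which the document offers no support. Allergic, febrile and respiratory reactions are already listed as expected (IX-1-1), and one early-treatment trial reported no adverse events (II-5-1). This stands.

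**Little depends on it.** X-3 treats secondary analyses as exploratory, and no stopping rule in X-5 is tied to this test. That limits the consequence but does not repair the endpoint.

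**As written, controls are not in the safety population at all (X-1-3).** This is a further conflict with X-3 rather than a defence. Once controls are restored so that the comparison can run, the asymmetry appears.

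**Conclusion.** The concern holds as a defect of definition. Endpoint 13 mixes Grade 3/4 events with unexpected events of any grade, and the second component has no stated control-arm reference. On the literal text it can add events only under plasma.

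A reader might go further and infer that the comparison is shown to be biased against plasma, with a high false-positive rate. The documents do not support that. Neither rate is given, the endpoint does not cite the product-based definition, and events meeting that definition are genuine reactions placed under the wrong label.

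The size is conditional on 170 per arm and a 3–5% Grade 3/4 rate: a chance of a significant excess of 2–3% at 0.5% extra events, about 6% at 1.3%, about 10% at 2% and 37–47% at 5%, against 1–2% with none. The effect is small at the low end and matters only if unexpected reactions are fairly common. It should be corrected because the wording is fixed in the protocol and costs little to change.

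**What to change.** 1. In III-2, III-4 and X-3, base the between-arm 72-hour count on events scored identically in both arms: Grade 3/4 adverse events, or SAEs as defined in IX-1-2, whatever their expectedness or relation to plasma. State which definition the Fisher and Poisson comparisons use.
2. Report unexpected reactions descriptively, in plasma recipients only, and leave the assessment of expectedness to safety reporting.
3. Reconcile X-1-3 with X-3 so that control patients are in the population used for the safety comparison.

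The cost is a wording amendment. Unexpected reactions are still collected and reported, and the sample size does not change.
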